## Abstract

**Background and motivation:**

The effectiveness of using acupuncture to treat migraine is rarely and even suspectedly reported in the literature. In this article, we report the design and the protocol of a randomized controlled large-scale trial to treat migraine using acupuncture, aiming at testifying it is effective to use acupuncture to treat migraine. We demonstrate also that the effectiveness of the treatment may vary due to using acupoints of different meridians or different acupoints of one meridian.

**Methods and design:**

A multi-center randomized controlled trial is currently undergoing, with three acupoints treatment groups and one non-acupoints control group. The acupuncture treatment consists of 20 sessions per patient with a observation period of 20 weeks. In total, 480 patients with Migraine are registered in this study within 8 hospitals in China from March 2008 to June 2009. These patients are randomly assigned to receive one of the following four acupoints treatment groups, i.e. 1) specific acupoints of Shaoyang meridians (120 patients), 2) non-specific acupoints of Shaoyang meridians (120 patients), 3) acupoints of other meridians (120 patients); or 4) non-acupoints control group (120 patients). The main outcome measurement in this trial is the effect comparison achieved among these four groups in terms of number of days with migraine and intensity of migraine during and after the baseline phase, i.e. the first 4 weeks before randomization and 4, 8 and 16 weeks after randomization. The intensity of headache including Headache intensity grade (0–3) and visual analogue scale (VAS) score will also be used in this study. In addition, the differences of Migraine-Specific Quality-of-Life Questionnaire (MSQ) and Transcranial Doppler Sonography (TCD) before and after randomization are also used as the secondary outcome measurement.

**Discussion:**

The result of this trial (which will be available in 2009) will demonstrate the efficacy of using acupuncture to treat migraine, and verify whether the specific effect of acupoints exists and whether this specific effect of acupoints is related to meridian and a collection of meridian Qi.

**Trials registration:**

Clinical Trials.gov NCT00599586

## Background

Migraine is a common disease. Population-based studies suggest that 6% to 7% of men and 15% to 18% of women experience migraine headache [1,2]. Acupuncture is gradually accepted as a complementary or alternative medicine for preventing migraine attack and relieving pain in countries beyond China, especially in the West. Recently, a randomized trial showed that acupuncture leads to persisting, clinically relevant benefits for patients with chronic headache, particularly migraine [3], which is consistent with many results reported in the previous literature on acupuncture for headache [4-6].

However, in recent years several randomized controlled trials argued that acupuncture was no more effective than sham acupuncture or minimal acupuncture in reducing migraine headache and tension-types of headache, although it was more effective than no treatment [7,8]. Convinced evidence for the efficacy of treating migraine with acupuncture is therefore inadequate because of these inconsistent results. In this multi-center randomized controlled large-scale trial, we firstly aim at investigating whether acupuncture is effective to treat migraine through a comparison with non-acupoints control. Secondly we investigate whether its efficacy is dissimilar due to using acupoints of different meridians or different acupoints of one meridian. The work reported in this article is financed by the National Basic Research Program (***973 Program***) in China, and is registered with an identifier (NCT00599586) by Clinical Trials.gov in the USA.

## Methods and design

### Design

This study is a multi-center randomized controlled trial comparing three acupoints treatment groups with one non-acupoint control group (fig. 1, fig 2). The design of this study followed the guidelines of the HIS Committee on Clinical Trails in Migraine [9]. The trial is completed in the following eight hospitals: First affiliated Hospital of Chengdu University of Traditional Chinese Medicine (TCM); People's Hospital of Sichuan province; No.4 People's Hospital of Sichuan province; Affiliated Hospital of Ningxia Medicine University; First affiliated Hospital of Hunan University of TCM; People's Hospital of Hunan province; No.1 People's Hospital of Wuhan City; TCM Hospital of Wuhan City.

**Figure 1 F1:**
[figure not shown]
Trial flow chart.

**Figure 2 F2:**
[figure not shown]
**Trial processes chart**. Note: VAS = visual analogue scale (0–10); MSQ = Migraine-Specific Quality-of-Life Questionnaire; Headache intensity grade: 0 = no headache; 1 = mild headache; 2 = moderate headache; 3 = severe headache; TCD = Transcranial Doppler Sonography.

The total observation period within this study is 20 weeks for each patient. All patients should have recorded headache diaries for 4 weeks before randomization (baseline phase). After randomization the patients will receive 20 sessions of 30 minutes' duration over a period of 4 weeks. All patients are asked to document their headache diaries, and the outcome measurement is completed both in the baseline and 4, 8 and 16 weeks after randomization.

The patients in the acupoints treatment groups and non-acupoint control group are blinded as to which treatment method they received. The patients will be nevertheless informed that they will receive either one of acupoints treatment groups or non-acupoint control group, which has been associated with positive outcome in clinical studies.

The central randomization is used in this trial, which is performed by the National Clinical Trial Center of Chinese Medicine, Chengdu, Good Clinical Practice (GCP) Center in China. The patients meeting the inclusion criteria will be randomly assigned to one of acupoints treatment groups or non-acupoint control group by the GCP Center through telephone, mobile phone, mobile message, or website, and a random number and group assignment will be immediately confirmed through email. This procedure assures that randomization will not be influenced, neither by the acupuncturists nor the patients.

This trial is performed according to the principles of the Declaration of Helsinki (Version Edinburgh 2000). And the trial protocol has been approved by local institutional review board and ethics committee. The written informed consent will be requested to sign for all of participants before registration. All patients will be given enough time to decide whether they would sign the informed consent, or they will be given treatment options other than acupuncture if they are not willing to participate.

### Patients

A power analysis is calculated before conducting this trial, which *α *= 0.05 and power = 90%. According to the previous literature [7], for the main outcome the number of days with migraine, an improvement of 2.4 days by sham acupuncture is reported. In this study, we anticipated an improvement of 4.0 days by acupuncture, so a difference of 1.6 days is considered minimally of clinical significance. Therefore, the sample size in this trial can be estimated initially according to the following formula [10]. Each group needs at least 120 patients (assuming a 15% dropout rate), 480 patients in four groups totally will be enrolled in the study.

$$n=\frac{\psi^{2}(\sum_{j=1}^{k}s_{j}^{2}/k)}{\sum_{j=1}^{k}{\left({\bar{x}}_{j}-\bar{\bar{x}}\right)}^{2}/(k-1)}$$

### Inclusion criteria

According to the criteria of the International Classification of Headache Society [11], patients who meet the diagnosis of migraine with or without aura will include in this study. The criteria are: 1)suffering from acute attacks of migraines for at least 1 year, with two or more migraine attacks per month during the last three months and during the baseline period; 2) between 18 and 65 years old with the onset age of migraine less than 50; 3)with baseline headache diary completed; 4) without using prophylactic drugs in the previous 1 month, 5) willing to finish 20 treatments in the following 4 weeks (acupuncture treatment period); and 6) with written consent form signed by themselves.

### Exclusion criteria

Patients with any of the following conditions will be excluded: headache caused by organic disorders, such as subarachnoid hemorrhage, cerebral hemorrhage, cerebral embolism, cerebral thrombosis, vascular malformation, arteritis, hypertension, arteriosclerosis, etc.; psychosis; pregnant women or women in lactation; patients with allergic constitution or easily getting infected or bleeding; or patients having taken drugs for preventing migraine in the last four weeks.

### Interventions

It took at least twelve months to develop the treatment strategies for this study. Interventions were according to records in ancient books and research results of modern papers about treating migraine with acupuncture in China or in the West, and were formed in consensus with Chinese acupuncturists and acupuncture experts, who come from both the study team and non-study team in all regions where the study is being conducted. In the first part of the clinical research of our ***973 project ***(accomplished in 2007), we confirmed the location of non-acupoints through compared one acupoints group with two non-acupoints control groups. The final strategies for this study are therefore defined as three acupoints treatment groups and one non-acupoints control group.

Based on the theory of TCM and acupuncture, migraine pertains to Shaoyang headache, and it has a close relationship with Shaoyang meridians, while it dose not relate to other meridians. Therefore, the effect of Shaoyang meridian is different from that of other meridians in acupuncture treatment of migraine. Additionally, in the same meridian, the effect of specific acupoints is different from the non-specific acupoints. Therefore, in our trial the three acupoints treatment groups are defined as 1) treatment group 1 (specific acupoints of Shaoyang meridians); 2) treatment group 2 (non-specific acupoints of Shaoyang meridians), and 3) treatment group 3 (acupoints of other meridians), and one non-acupoints control group.

#### Treatment group 1

Waiguan (TE5), Yanglingquan (GB34), Qiuxu (GB40), Fengchi (GB20) are punctured by filiform needles unilaterally. Waiguan (TE5) is punctured perpendicularly 0.5–1 cun. Yanglingquan (GB34) is punctured perpendicularly 1–1.5 cun. Qiuxu (GB40) is punctured perpendicularly 0.5–0.8 cun. Fengchi (GB20) is punctured obliquely 0.8–1.2 cun, the tip of needle towards the tip of the nose.

#### Treatment group 2

Luxi (TE19), Sanyangluo (TE8), Xiyangguan (GB33), Diwuhui (GB42) are punctured by filiform needles unilaterally. Luxi (TE19) is punctured transversely 0.3–0.5 cun. Sanyangluo (TE8) is punctured perpendicularly 0.5–1 cun. Xiyangguan (GB33) is punctured perpendicularly 1–1.5 cun. Diwuhui (GB42) is punctured perpendicularly 0.5–0.8 cun.

#### Treatment group 3

Touwei (ST8), Pianli (LI6), Zusanli (ST36), Chongyang (ST42) are punctured by filiform needles unilaterally. Touwei (ST8) is punctured transversely 0.5–1.0 cun. Pianli (LI6) is punctured perpendicularly 0.3–0.5 cun. Zusanli (ST36) is punctured perpendicularly 1–2 cun. Chongyang (ST42) is punctured perpendicularly 0.3–0.5 cun, avoid needling the artery.

#### Control group

In the medial arm on the anterior border of the insertion of the deltoid muscle at the junction of deltoid and biceps muscles [12], is punctured perpendicularly 0.5–1 cun. The edge of tibia 1 to 2 cm lateral to the Zusanli (ST36) horizontally [13], is punctured perpendicularly 0.5–1 cun. Half between the tip of the elbow and the axilla [14], is punctured perpendicularly 0.5–1 cun. Ulnar side, half between epicondylus medialis of the humerus and ulnar side of the wrist [14], is punctured perpendicularly 0.5–1 cun. All non-acupoints are punctured by filiform needles unilaterally.

In each session all acupoints and non-acupoints are punctured by filiform needles unilaterally, and left and right side are alternatively used. After 4 acupoints or non-acupoints being needled, 4 auxiliary needles will be punctured at 2 mm lateral to every acupoint or non-acupoint and punctured to a depth of 2 mm without manual stimulation. Transcutaneous electric acupoint stimulation (HANS: Han's acupoint nerve stimulator, HANS-200, made in Nanjing, China) is used for electro-acupuncture stimulation at every acupoint or non-acupoint after needle insertion. Each acupuncture needle of acupoints or non-acupoints and its auxiliary needle are connected with the electricity by HANS for 30 minutes. The stimulation frequency is 2/100 Hz. The stimulation intensity varied from 0.1 mA to 1.0 mA until the patients feel comfortable.

The filiform needles are used in this trial, which are sterile acupuncture needles for single use; namely Hwato Needles, made in Suzhou, China, 25–40 mm in length and 0.25 mm in diameter. The needles with 13 mm in length and 0.18 mm in diameter especially are used as auxiliary needle without manipulating the needles. The acupoints of the treatment groups are asked to achieve DeQi sensation by lifting and thrusting combined with twirling and rotating the needles, but the non-acupoints of control group are not asked to achieve DeQi sensation by the same manipulating the needles. Both the treatment groups and control group are asked to retain the needles for 30 minutes, and close the acupoint holes with clean cotton balls to avoid bleeding when withdrawing the needle.

All patients will receive 20 treatments totally over a period of 4 weeks, once a day, five times continuously and two days interval in a week.

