### Statistical analysis

Analysis of all data in this trial will be performed by the National Clinical Trial Center of Chinese Medicine (Chengdu GCP Center) in China, which is performed in a blinded manner because analysis of data is done by a special analysis-researcher. The data will be analyzed with SPSS13.0 and SAS9.0 statistical software packages.

The intention-to-treat (ITT) population is defined as the patients who are randomized. The data analysis of baseline characteristics is based on the intention-to-treat (ITT) population. And the data analysis of the primary and secondary outcomes and other outcomes is mainly based on the intention-to-treat (ITT) population. In addition the per-protocol (PP) population is analyzed. The result of the ITT analysis will be compared with that of the PP analysis to check whether the results are consistent.

The first step of analysis is to make comparisons among baseline characteristics in different groups. The second step is to check whether acupoints treatment groups were more efficacious in treating migraine than non-acupoints control group. If acupoints treatment is more effective than non-acupoints treatment in treating migraine, the third step is to make comparisons among three acupoints treatment groups in effectiveness of treating migraine.

For normal distribution data (normality, homogeneity of variances) the repeated measures analysis will be used in the different time-points assessment. The Kruskal-Wallis test will be employed in the analysis of skewed distribution data. Moreover, analysis of variance (ANOVA) and used for numerical variables, Chi-square test is used for categorical variables. Two-sided test is applied for all available data, and a P value < 0.05 is considered statistically significant.

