According to the theory of TCM and acupuncture, there is no doubt that the differences between acupoints and non-acupoints in specific physiological effects do exist. Acupuncture has also been recognized as a method for treating many diseases, not only widely in China due to its long history in clinical practice, but also gradually in many western countries due to its increasing popularity. However, in recent years diverse observations about 'specific' and 'unspecific' effects of acupoints have also been experienced by a few clinical trials in the West. For instance, a randomized controlled trial illustrated from their study that acupuncture was no more effective than sham acupuncture or minimal acupuncture in reducing migraine headache and tension-types of headache, despite its effectiveness compared with no treatment [7,8]. Their results suspected that acupuncture effect may be due to unspecific physiology effects of needling, to a powerful placebo effect, or to a combination of both [7]. We argue, however, through our early investigation and the undergoing multi-center randomized controlled large-scale trial, that acupuncture does have effect in treating migraine. Through the reported studies in this article, we examine the efficacy of acupuncture for treating migraine to large samples of patients. Furthermore, we investigate whether the different efficacy of three acupoints treatment groups is due to the acupoints of different meridians or different acupoints of one meridian. We believe this trial could demonstrate that the efficacy of using acupuncture to treat migraine is *not *due to physiological effects of acupoints suspected in [7], but the real 'specific effects' of acupoints based on meridians and a collection of meridian Qi.

Central randomization is used in our trial, which is a strict, complete randomization, and ensures adequate concealment. During the whole trial period, the patients are not aware of which group they belong to, but they do know they will receive acupuncture needling treatments by either puncturing different acupoints or puncturing non-acupoints.

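### The acupoint groups are needled to DeQi and the control is not, so the second-step comparison tests a treatment package and cannot by itself verify a point-specific effect

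*Protocol article*

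**What the plan says.** The Control group subsection of Interventions sets the manual technique for all arms. For groups 1 to 3: "The acupoints of the treatment groups are asked to achieve DeQi sensation by lifting and thrusting combined with twirling and rotating the needles". For the control: "the non-acupoints of control group are not asked to achieve DeQi sensation by the same manipulating the needles".

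Much else is common to all four arms. On electrical stimulation: "Each acupuncture needle of acupoints or non-acupoints and its auxiliary needle are connected with the electricity by HANS for 30 minutes". On retention: "Both the treatment groups and control group are asked to retain the needles for 30 minutes". Four sites per session, four auxiliary needles and 20 sessions over 4 weeks also apply to everyone.

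The Background states the first aim: "we firstly aim at investigating whether acupuncture is effective to treat migraine through a comparison with non-acupoints control". The Statistical analysis section puts this into practice: "The second step is to check whether acupoints treatment groups were more efficacious in treating migraine than non-acupoints control group". If that succeeds, a third step compares the three acupoint groups with each other.

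The conclusions announced go further. The abstract's Discussion says that the result will "verify whether the specific effect of acupoints exists and whether this specific effect of acupoints is related to meridian". The Discussions section expects to show that the benefit reflects "the real 'specific effects' of acupoints based on meridians and a collection of meridian Qi", in answer to earlier trials that suggested a non-specific physiological response to needling, placebo, or both. Its closing paragraph repeats that purpose.

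**The concern.** A comparison supports a claim about needle location only if location is what differs between the arms, or if other differences can be separated out. Here a second difference, whether DeQi is sought by manipulation, follows the same dividing line. It is also close to the rival explanation that the article sets out to refute: more vigorous needling on one side leaves a non-specific response to needling open as the cause of a difference.

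At stake is what may be concluded from a significant second step. The article commits itself in advance to an interpretation that the comparison cannot deliver alone.

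**Working it through.** **1. What the arms identify.** Cross location with stimulation target, using the Interventions section:

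| | DeQi sought | DeQi not sought |
|---|---|---|
| Acupoint | Groups 1, 2, 3 | no arm |
| Non-acupoint | no arm | Control |

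Two of the four cells are empty. Write L for the effect of location, D for the effect of seeking DeQi, and I for any interaction. Then:

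- Second step: acupoint group minus control = L + D + I. This is one contrast with at least two unknowns, so no analysis of these data recovers L.
- Third step: group i minus group j. The DeQi instruction is the same on both sides, so a common D cancels. No term compares an acupoint with a non-acupoint.

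The control sentence is loosely worded. It may mean no manipulation, or the same manipulation without a DeQi target. The target differs between arms on either reading, so D stays in the contrast.

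**2. What each result would mean.**

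- Positive second step: the package with DeQi sought outperforms the control package. This answers the first aim as the Background frames it. It does not say whether L, D or both are responsible.
- Null second step: no difference was shown between two needled and electrically stimulated treatments. That is not evidence that acupuncture is ineffective.

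**3. Illustration of size.** The Patients section gives alpha 0.05, power 90%, a difference of 4.0 − 2.4 = 1.6 days, 15% dropout and 120 per group. It gives no standard deviation and no means for the separate acupoint groups, so 120 cannot be reproduced. Evaluable patients: 120 × (1 − 0.15) = 102 per group. Solving the two-mean formula for the SD that gives 90% power:

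SD = 1.6 / [(1.960 + 1.282) × √(2/102)] ≈ 3.5 days

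This SD is an assumption, and I take 3.0 to 4.0 as a range. The Statistical analysis section does not say whether the acupoint groups are pooled, so I compare one acupoint group with control, 102 against 102. Set the location effect to zero and let seeking DeQi alone be worth d days. The chance of a significant result favouring acupoints is Φ(d / (SD × √(2/102)) − 1.96):

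| d (days) | SD 3.0 | SD 3.5 | SD 4.0 |
|---|---|---|---|
| 0.8 | 0.48 | 0.37 | 0.30 |
| 1.2 | 0.82 | 0.69 | 0.57 |
| 1.6 | 0.97 | 0.90 | 0.82 |

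The 0.90 at d = 1.6 and SD 3.5 is the design power by construction. The comparison responds to a stimulation effect exactly as it would to a location effect of the same size. The article does not say how large d is, so the table shows that the two cannot be told apart, not that a bias is present.

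**The case against.** The strongest reply is that the analysis rule is already narrow. The second step only asks whether the acupoint groups do better than the non-acupoint control; it does not say that this alone proves specificity. The broad statements sit in discussion prose and describe the whole trial, including the third step. This stands as to where the fault lies: in the stated conclusions, not in a test or decision rule. It does not remove the fault, because the third step has no non-acupoint arm and so cannot supply the missing evidence that a point-specific effect exists.

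One could also treat DeQi as part of what acupoint treatment is. That would make the second step a coherent package comparison, but the article frames specificity by points, meridians and meridian Qi and nowhere defines it to include DeQi.

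A reader might infer several stronger points that the article does not support:

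- *That the second step cannot answer the first aim.* The Background defines that aim as a comparison with the non-acupoint control, and the second step makes that comparison. The article does not claim that it tests acupuncture against no treatment, and the Discussions section assigns basic efficacy to the first part of the project.
- *That patients are unblinded.* The article says that patients are blinded, and shared electrical stimulation, auxiliary needles and retention time may mask differences in sensation. Unblinding is conjecture.
- *That a pooled contrast of 360 against 120 is affected.* Pooling is not stated.
- *That the third step should be freed from the second.* That would alter the testing sequence and raise multiplicity, which is a separate question.
- *That the control sites lying on arm and leg are a further confounder.* This is itself a difference in location, so it is not clearly distinct from the factor under test.

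**Conclusion.** The concern holds for the attribution of a second-step difference to point location. The Control group subsection and the specificity statements in the abstract's Discussion and the Discussions section do not fit together and need to be reconciled. Every acupoint versus non-acupoint comparison in the trial carries the DeQi difference. How much of an observed effect it could explain cannot be estimated from the article; the figures above rest on an assumed SD, an assumed DeQi effect and unpooled groups.

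The contrasts among groups 1, 2 and 3 share the DeQi instruction and are free of this particular difference, although needle depth and angle also vary between those groups. This should be corrected, but it is a fault of interpretation: no figure, test or primary analysis is shown to be wrong.

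**What to change.** State the second-step conclusion as a comparison of acupoint electro-acupuncture with DeQi sought against non-acupoint electro-acupuncture without DeQi sought, and attribute nothing in it to point location. Say that a null result would not show acupuncture to be ineffective.

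Draw conclusions about choice of points or meridian from the contrasts among groups 1, 2 and 3, within the existing testing sequence. Acknowledge that these contain no non-acupoint arm, so this design does not isolate location specificity of acupoints against non-acupoints. Amend the abstract's Discussion and the Discussions section, including its closing paragraph, to match.

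The cost is a change of wording and a narrower headline claim. No change to needling, sample size or analysis is proposed.
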